### Data analysis

2.8

All data will be entered into IBM Statistical Packages for Social Sciences (SPSS) version 25.0. Intention-to-treat (ITT) method will be used; all the participants recruited at baseline will be included in the outcome analysis. Using ITT, missing data will be replaced with last observation carried forward. Socio-demography and health profile of the participants will be analyzed descriptively and reported as frequencies (percentages) and mean (standard deviation) or median (inter-quartile range). The effects of the interventions will be analyzed using mixed model ANOVA and reported as main time, group, and time–group interaction effects. The level of significance will be set as *P* < .05 for all results.

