**Methods::**

This is an assessor blinded randomized controlled trial comparing 2 intervention approaches namely ART-added physiotherapy (experimental group) and usual physiotherapy (control group). A total of 70 post-stroke patients will be recruited and allocated into either the ART-added physiotherapy or the usual physiotherapy group. The ART-added physiotherapy group will undergo a 20-minute ART session followed by 40 minutes of usual physiotherapy. While the usual physiotherapy group will receive usual physiotherapy alone for 60 minutes. All participants will be treated once a week and are required to carry out a set of home exercises for 2 times per week during the 12-week intervention. Assessment of emotional status and functional independence will be carried out at pre-intervention and week 13 of the intervention with the use of Hospital anxiety and depression scale, Barthel index, and EuroQol-5 dimensions-5 levels. All data will be analyzed using descriptive and inferential statistics.

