### Study participants

2.2

The study participants will be selected with the assistance from physiotherapists in Universiti Kebangsaan Malaysia Medical Centre (UKMMC) using a simple random sampling method from stroke patients’ registry which is maintained by the rehabilitation unit of the hospital.

The inclusion criteria are as follows:

First-time stroke, diagnosed clinically by a medical physician.Sub-acute phase post-stroke (2 weeks–3 months), medically stable condition.Age 40 to 75 years.Montreal cognitive assessment score ≥26.

The exclusion criteria are:

Having receptive aphasia.History of any psychosomatic disorders.Score ≥4 on a modified Rankin scale (wheelchair or bed bound).

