### Interventions

2.4

The experimental group will receive ART session for 20 minutes, followed by usual physiotherapy for 40 minutes. The ART will be conducted in a quiet room. Participants will be positioned in supine lying or sitting throughout the session and should empty his or her bladder before the session. During the ART session, the participants are asked to loosen any tight clothing, remove watch, spectacles, and stockings. The participants are allowed to close their eyes but not fall asleep while listening to the ART instructions.

Generally, there are 6 standard exercise tasks in ART:

Tranquility exercise: should create a state of silence and concentration. Typical imagination: “I am calm. Nothing can disturb me.”Heaviness exercise: should create a sense of heaviness in the limbs. Typical imagination: “My arms and legs are heavy.”Warmth exercise: sense of heat in the limbs. Typical imagination: “My arms and legs are warm.”Breathing exercise: concentrated breathing. Typical imagination: “My breath is calm and regular.”Heart exercise: Should cause further sedation. Typical imagination: “My heart beats calmly and regularly.”Solar plexus exercise: concentration on the celiac plexus should deepen the relaxation. Typical imagination: “The center is warm.”

After the ART session, the participants will be asked to remain on the training mat for 5 minutes before starting usual physiotherapy interventions. Usual physiotherapy in this study consists of general functional exercises, balance, upper limb, and gait training.

The control group will undergo usual physiotherapy alone for 60 minutes. The content of usual physiotherapy is similar to that given to the ART-added physiotherapy group. Blood pressure of each participant will be recorded before and after the intervention session. The participants are instructed to report any unusual feelings that they may experience such as giddiness, nausea, or shortness of breath to the physiotherapist during the intervention sessions.

Both groups undergo the given intervention for 3 times per week (1 supervised and 2 non-supervised) for 12 weeks, for a total duration of 1 hour per session. Monitoring of the participants will be done weekly during the supervised session to ensure adherence to the non-supervised in-home sessions and to assess the occurrence of any adverse effect.

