### Assessment of outcomes

2.6

Participants will be assessed at baseline and at week 13 of interventions by a therapist who is blinded to the group allocation and trained to conduct the standardized tests. The recorded baseline assessment data will not be accessible to the blinded assessor at post-trial assessment in view to avoid assessment bias.

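### With outcomes scored only at baseline and week 13, last observation carried forward enters every missing final score as zero change; the bias depends on how many are lost, in which arm, and how much patients recover

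*Protocol article*

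**What the plan says.** Section 2.8 (Data analysis) adopts intention-to-treat, under which "all the participants recruited at baseline will be included in the outcome analysis", and sets the rule for gaps: "Using ITT, missing data will be replaced with last observation carried forward". Effects are to be "analyzed using mixed model ANOVA and reported as main time, group, and time–group interaction effects".

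Section 2.6 (Assessment of outcomes) gives two time points: "Participants will be assessed at baseline and at week 13 of interventions". The Methods paragraph of the abstract agrees: assessment "will be carried out at pre-intervention and week 13 of the intervention".

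Section 2.4 (Interventions) adds a weekly contact, described as "Monitoring of the participants will be done weekly during the supervised session to ensure adherence to the non-supervised in-home sessions" and for picking up adverse effects. No HADS, Barthel or EQ-5D-5L score is scheduled at that contact.

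Entry under section 2.2 requires "Sub-acute phase post-stroke (2 weeks–3 months), medically stable condition". Section 2.9 lets participants withdraw at any time. The article gives no expected loss rate.

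**The concern.** Carrying a value forward needs an earlier post-baseline value. Here there is none, so the rule is baseline carried forward. Everyone without a week-13 score enters the time–group interaction with a change of exactly zero, and the model treats that zero as measured.

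Zero is a doubtful value for this population. Patients join 2 weeks to 3 months after a first stroke and both arms receive 12 weeks of physiotherapy, so some change can be expected, most clearly in functional independence. If both arms improve, the rule penalises whichever arm loses more people. At stake are the size of the treatment estimate, the power to detect it and, when losses differ by arm, the type I error. The rule applies to every outcome. It is a definite instruction, not a detail left open for an analysis plan.

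**Working it through.** **The plan's own figure.** Section 2.7 gives 70 participants, effect size 0.34, 80% power and a 5% level. Reading 0.34 as Cohen's f in a two-group F test, the noncentrality is 0.34² × 70 = 8.09 on (1, 68) degrees of freedom, and power is 0.801. Reading it as d (f = 0.17) for the interaction with two measures correlated 0.5, the noncentrality is 0.17² × 70 × 2/(1 − 0.5) = 8.09, again 0.801. The total of 70 reproduces both ways, so the text does not settle the metric. I use the first reading, a difference of 2 × 0.34 = 0.68 SD.

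**Inputs.** From the article: two visits, the carry-forward rule, total 70. Assumed: 35 per arm, correlation 0.5, loss of 10–30% per arm unrelated to outcome, recovery in both arms of 0, 0.5 or 1 SD. With correlation 0.5 the variance of change is 2(1 − 0.5) = 1, so change is in the same SD units. Positive means improvement.

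**Expected estimate.** With two visits, the interaction test is a comparison of mean change. Let d be the share lost and mu the true mean change, for ART (T) and control (C). Under the rule:

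estimate = (1 − dT)·muT − (1 − dC)·muC

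- Equal loss d: estimate = (1 − d)(muT − muC). At 10%, 0.68 × 0.9 = 0.61; at 20%, 0.68 × 0.8 = 0.54. If 0.34 were itself the SD difference, 0.34 × 0.8 = 0.27, the same proportional shrinkage.
- No true effect, both arms recovering by mu: estimate = mu(dC − dT). This is zero when losses are equal.

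**Power at 20% loss per arm, true effect 0.68 SD.** In each arm the variance of change under the rule is (1 − d) + d(1 − d)mu². Power is approximately Φ(estimate/SE − 1.995), with 1.995 the t quantile on 68 degrees of freedom.

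| Recovery | Variance, ART + control | SE | 0.544/SE | Power by formula | Power by simulation |
|---|---|---|---|---|---|
| 0 | 0.874 + 0.800 | 0.219 | 2.49 | 69% | about 70% |
| 0.5 SD | 1.023 + 0.840 | 0.231 | 2.36 | 64% | about 64% |
| 1 SD | 1.252 + 0.960 | 0.251 | 2.16 | 57% | about 57% |

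The like-for-like comparator is change scores in the 28 per arm who are observed: SE = √(2/28) = 0.267 and 0.68/0.267 = 2.54, giving power of about 70% whatever the recovery. The rule itself therefore costs about 0, 5 and 13 points. Separately, adjusting for baseline (ANCOVA on observed data) raises power to about 81%.

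**No true effect, 10% lost in ART, more lost in control.** Bias is mu(dC − dT); type I error is from simulation with losses drawn at random.

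| Lost in control | Bias, 0.5 SD recovery | Type I error | Bias, 1 SD recovery | Type I error |
|---|---|---|---|---|
| 15% | 0.03 SD | 5% | 0.05 SD | 6% |
| 20% | 0.05 SD | 6% | 0.10 SD | 7% |
| 25% | 0.08 SD | 6% | 0.15 SD | 10% |
| 30% | 0.10 SD | 8% | 0.20 SD | 14% |

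Swapping the arms reverses the sign. Observed-case change scores stay near 5% throughout. If the numbers lost are held fixed, the 1 SD errors in the last two rows fall to about 7.5% and 9–10%.

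**The case against.** The mechanism is hard to dispute; the size is not. Four stronger readings are tempting, and the article does not support them.

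- **That losses will be large.** A reader might take the Introduction's 65% of survivors who do not adhere to exercises as a forecast of missing data. That figure concerns exercise adherence. A non-adherent participant can still be assessed at week 13, and there is weekly contact. The relevant text is section 2.9, which shows only that loss can occur.
- **That the whole gap between 57–70% and about 81% power is the price of the rule.** That comparison changes the missing-data method and the baseline adjustment together. With no recovery, the entire gap comes from baseline adjustment.
- **That the comparison is always biased.** Under outcome-unrelated loss, equal losses with no true effect give no bias and a type I error near 5%. Appreciable inflation needs both substantial recovery and a marked imbalance in losses.
- **That zero change is implausible on every scale.** The entry window states a time since stroke, not an amount of recovery. The Introduction speaks of emotional consequences persisting, and no HADS threshold is set for entry. Expected change is easier to defend for function than for mood.

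It might also be said that the rule is conservative or that intention-to-treat requires it. Neither stands. It is not conservative when control loses more, and intention-to-treat requires analysis as randomised, not single imputation.

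**Conclusion.** The defect holds and follows directly from two explicit statements, the carry-forward rule and the two-visit schedule. At 20% loss per arm a true effect shrinks by one fifth, and power falls by about 0 to 13 points depending on recovery. When there is no effect, unequal loss produces a spurious difference of 0.03–0.20 SD over the range examined, with type I error from about 5% to 14%. These sizes rest on assumed loss and recovery, loss unrelated to outcome, equal arms and a correlation of 0.5; the 0.68 SD is one of two readings of the stated 0.34. Because the harm is conditional on those quantities, this is a point that should be fixed rather than one that by itself undermines the trial.

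**What to change.** Replace the carry-forward sentence in section 2.8 with wording such as:

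> All randomised participants are analysed as allocated with a likelihood-based model valid under missing-at-random (a mixed model for repeated measures using all available scores, or ANCOVA on the week-13 score adjusted for baseline after multiple imputation). Last observation carried forward is reported only as a sensitivity analysis.

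One of the two options should be named before the data are seen. The power of about 81% shown above was calculated for observed-data ANCOVA and should not be assumed for an unadjusted mixed model.

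The cost is protocol wording and slightly more analysis work, with no new visits or participants. The downside is reliance on missing-at-random, which cannot be verified from the data and should be probed by sensitivity analysis.

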### Outcomes

2.5

Feasibility of the intervention will be assessed with regards to the participants’ acceptance and adherence, the occurrence of adverse effect and feedback from the participants.

Outcomes of the main study will be measured as follows:

The anxiety level will be measured using Hospital anxiety and depression scale (HADS), a self-reported questionnaire and most reliable instrument to identify the presence of depression and anxiety in outpatient department.^[25]^ The scoring can be classified as normal (0–7), borderline (8–10), and caseness (≥11).^[26]^ The recommended cut off score for Hospital anxiety and depression scale is ≥8. The tool has established validity and reliability, with a reliability score of 0.88 for anxiety subscale and 0.79 for depression subscale.Modified Barthel index (MBI) will be used to measure functional independence of the participants. MBI is a tool to measure the degree of assistance needed by a person, with using 10 specific activities of daily living. Each component is scored by numerical scale and the total score ranges from 0 to 20. The classification is based on physical disability; no physical disability (20), mild impairments (15–19), moderately disabled (10–14), severe disability (5–9), and very severely disabled (0–4). MBI demonstrates high test-retest reliability and inter-rater reliability.^[27,28]^EuroQol 5-Dimension 5 Levels (EQ5D5L), a standardized instrument for measuring generic health status will be used to measure quality of life of the participants. The descriptive system comprises 5 dimensions of life namely mobility, self-care, usual activities, pain/discomfort, and anxiety/depression. Each dimension has 5 levels of response: no problems, slight problems, moderate problems, severe problems, and extreme problems. The respondent is asked to indicate his/her health state by ticking (or placing a cross) in the box against the most appropriate statement in each of the 5 dimensions. This response results in a 1-diginumber expressing the level selected for that dimension. The digits for 5 dimensions can be combined in a 5-digit number describing the respondent's health state, termed health utility index. All dimensions of the EQ5D5L are reliable in test–retest with intraclass correlations ranging from 0.67 to 0.81.^[29]^

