## Discussion

3

The main aim of the study is to assess the effectiveness of autogenic relaxation training in addition to usual physiotherapy in comparison to usual physiotherapy alone in reducing emotional disturbances and improve functional level of stroke survivors in the community. Ensuring regular participation of stroke survivors in the rehabilitation is a challenging task and poor participation negatively affects post-stroke recovery. As a facilitator of physical activity, the physiotherapists need to encourage their involvement in rehabilitation and adherence towards the prescribed exercise program. Currently, there is no intervention which has been incorporated in the field of stroke physiotherapy, which influences the emotion and motivation level of stroke survivors.

Although emotional issues are significant post-stroke,^[32–34]^ the use of ART in stroke population has not been well explored. A study conducted on patients with post-stroke anxiety showed significant changes in the HADS after the administration of ART.^[23]^ However, the authors pointed out that the study has many limitations such as small sample size and lack of blinding. Another study conducted to assess self-reported tension in post-stroke patients using tension rating circles also observed potential changes after ART.^[24]^ There were several practical difficulties which emerged during their study especially in ART session management, staffing resources, and awareness of attendance criteria. Nonetheless, the participants reported greater self-motivation after the ART session.

The 2 studies^[23,24]^ considered mainly the effectiveness of ART on post-stroke anxiety. Changes in motor performance as a result of psychological improvement among the stroke survivors following ART were not studied. This proposed study will analyze the effect of physiotherapist-mediated ART on anxiety and functional independence. The results of the study will provide the information on the functionality and quality of life among those who has anxiety and how this change following ART and physiotherapy. The study will also assess the feasibility of setting up a relaxation group protocol to handle post-stroke anxiety in an out-patient rehabilitation setting. This will help to fill the gap in the field of ART usage on mental state and motor performance among stroke population.

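### The article ranks no outcome but applies an unadjusted .05 to every result, so the chance of a false positive treatment claim is about 11–19% rather than 5%, and the sample size names no outcome

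*Protocol article*

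**What the plan says.** Section 2.5 (Outcomes) opens with "Outcomes of the main study will be measured as follows" and then describes the HADS, the MBI and the EQ-5D-5L in turn. None is called primary or secondary. The abstract is equally neutral: assessment is "with the use of Hospital anxiety and depression scale, Barthel index, and EuroQol-5 dimensions-5 levels".

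The target is worded differently from place to place:
- Section 2.5 ties the HADS to anxiety: "The anxiety level will be measured using Hospital anxiety and depression scale (HADS), a self-reported questionnaire". Its reliability is then given for both parts, "with a reliability score of 0.88 for anxiety subscale and 0.79 for depression subscale".
- The Discussion gives a joint main aim, "in reducing emotional disturbances and improve functional level of stroke survivors in the community".
- The Discussion later says "This proposed study will analyze the effect of physiotherapist-mediated ART on anxiety and functional independence", and its closing paragraph anticipates benefit on anxiety, function and quality of life together.

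Section 2.8 (Data analysis) prescribes a mixed-model ANOVA, "reported as main time, group, and time–group interaction effects", and sets the threshold: "The level of significance will be set as *P* < .05 for all results".

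Section 2.7 (Sample size) gives 70 participants from a mixed-model ANOVA calculation with effect size 0.34, significance level .05 and 80% power. The 0.34 comes from a cited source. The section does not say which outcome it describes, whether it is Cohen's f or d, or which ANOVA effect is powered.

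**The concern.** Three or four scores are tested at .05 each with no order among them, in a trial that sets out to establish effectiveness. The 5% error rate then holds for each test but not for the trial's conclusion, because a significant result on any scale could be put forward as showing that autogenic relaxation training works.

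The sample size does not settle which result counts. If 0.34 were tied to a named score and a named effect, a reader could infer the primary test from it. As written, the 80% power belongs to no identifiable claim.

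This is more than detail left to a fuller document. The article states a rule for all results, and a hierarchy or adjustment held elsewhere would contradict that sentence. The wording needs correcting either way.

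**Working it through.** **Inputs from the article.** Three instruments (section 2.5). The HADS has two subscales, so there are four scores if both are analysed. Three ANOVA effects per score and .05 throughout (section 2.8). Two measurements, baseline and week 13 (section 2.6). N = 70, effect size 0.34, 80% power (section 2.7).

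**Assumptions, not in the article.** 1:1 allocation. Between-scale correlation from 0 to 0.7. For the mixed ANOVA, a within-person correlation of 0.5.

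**Step 1: the plan's own figure.** Power comes from the noncentral F distribution with 1 and N − 2 = 68 degrees of freedom.
- Reading (a): 0.34 is d, so f = 0.34/2 = 0.17, for the time-by-group interaction. The noncentrality is f² × N × 2/(1 − 0.5) = 0.0289 × 70 × 4 = 8.09. Power is 0.801, and the smallest N is 70.
- Reading (b): 0.34 is f in a two-group comparison of a single measure. The noncentrality is f² × N = 0.1156 × 70 = 8.09. Power is again 0.801 and N = 70.
- Other readings give other sizes. With f = 0.34 and within-person correlation 0.5, the interaction needs 20 and the between-group effect needs 54. With d = 0.34 in a plain two-sample t test, 274 are needed.

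So N = 70 is reproducible, but only after the reader chooses the metric and the effect. Neither choice reveals the outcome.

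**Step 2: chance of at least one false positive, time-by-group test only.** Under independence this is 1 − 0.95^k:
- k = 3: 1 − 0.8574 = 0.143
- k = 4: 1 − 0.8145 = 0.185

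For correlated scales, 1,000,000 sets of equally correlated normal statistics were simulated, and a set was counted if any absolute value exceeded 1.96.

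| Between-scale correlation | Three scales | Four scores |
|---|---|---|
| 0 | 14.3% | 18.5% |
| 0.3 | 13.6% | 17.4% |
| 0.5 | 12.5% | 15.6% |
| 0.7 | 10.9% | 13.1% |

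Against 5%, that is 10.9/5 = 2.2 to 14.3/5 = 2.9 times for three scales, and 13.1/5 = 2.6 to 18.5/5 = 3.7 times for four scores.

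**Step 3: what each remedy does to power.**
- One primary outcome with one effect at .05 leaves the error rate at 5% and power at 0.801 with N = 70, provided 0.34 applies to that outcome as in (a) or (b).
- Keeping every scale confirmatory with Bonferroni means .05/3 = .0167 or .05/4 = .0125 per test. At the same noncentrality of 8.09, power at N = 70 falls to 0.65 or 0.61. Restoring 80% takes 94 or 100 participants (reading b).

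**The case against.** **A condensed article.** It may leave a primary outcome to the full protocol or the registration, neither of which can be seen here. That stands as a limit on the claim. A reader might infer that the trial has no primary outcome, but the documents show only that this article ranks none. The objection does not rescue the sentence that sets .05 for all results, because that is a positive statement.

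**A per-test threshold is not a success rule.** This is fair: the article nowhere says that a single significant scale proves effectiveness. It also says nothing to prevent that reading, and its main aim is joint.

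**A larger error rate.** A reader might add the group main effect and reach 1 − 0.95^8 = 34% for eight tests. The documents do not support that as the headline:
- The group main effect averages baseline with week 13 and is not the natural treatment test in this design.
- Four scores is itself an assumption, since section 2.5 assigns the HADS to anxiety.
- Independence is doubtful, since the EQ-5D-5L has items on mobility, self-care and anxiety/depression that overlap with the other two scales.
- Time effects should not be counted at all. Recovery in both arms would make them real, and they do not compare treatments.

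**The sample size.** A reader might infer that N = 70 or the 80% power is wrong. It is not shown to be: 70 reproduces, and the power holds for whatever outcome and effect 0.34 describes.

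**The method of analysis.** A switch to ANCOVA is not needed. The mixed ANOVA does not cause the multiplicity, and naming its interaction on one outcome cures it.

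**Conclusion.** The concern holds within limits. The article ranks no outcome and fixes an unadjusted .05 for all results. With no true effect on any scale, the chance of at least one significant time-by-group result is 10.9–14.3% for three scales and 13.1–18.5% for four scores. These ranges rest on an assumed between-scale correlation of 0.7 down to independence. The four-score range also assumes that both HADS subscales are analysed.

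The sample size figure is unattached, not wrong. The correction should be made, and it is cheap.

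**What to change.** Before outcome data are seen:

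1. Name one primary outcome and one effect in sections 2.5 and 2.8. One candidate is the HADS anxiety score, which section 2.5 lists first, with the between-arm difference in change from baseline to week 13 (the time-by-group effect), tested at two-sided .05. The choice is the sponsor's, given the joint aim in the Discussion.
2. State in section 2.7 that 0.34 and N = 70 refer to that outcome and effect. Give the metric and, if the interaction is powered, the assumed within-person correlation. If 0.34 does not describe that outcome, redo the calculation.
3. Make the remaining scales secondary. Test them only after a significant primary result, in a fixed order or by Holm, or report them as supportive. Say whether the HADS depression score is among them.
4. State that time and group main effects are descriptive and are not evidence of effectiveness.
5. Replace the blanket .05 sentence in section 2.8 with this rule.

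The cost is wording and stricter claims on the secondary outcomes. N = 70 can stay if 0.34 applies to the chosen outcome. If the sponsor prefers to keep all scales confirmatory with Bonferroni, the power statement should be revised to about 0.65 (three scales) or 0.61 (four scores) at N = 70, or the size raised to about 94 or 100.
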